## Abstract

**Background:**

Premature birth is considered one of the main problems in modern Obstetrics. It causes more than 50 % of neonatal mortality; it is responsible for a large proportion of infant morbidity and incurs very high economic costs. Cervical length, which can be accurately measured by ultrasound, has an inverse relationship with the risk of preterm birth. As a result, having an effective intervention for asymptomatic patients with short cervix could reduce the prematurity. Although recently published data demonstrates the effectiveness of vaginal progesterone and cervical pessary, these treatments have never been compared to one another.

**Methods/Design:**

The PESAPRO study is a noncommercial, multicenter, open-label, randomized clinical trial (RCT) in pregnant women with a short cervix as identified by transvaginal ultrasonography at 19 to 22 weeks of gestation. Patients are randomized (1:1) to either daily vaginal progesterone or cervical pessary until the 37th week of gestation or delivery; whichever comes first. During the trial, women visit every 4 weeks for routine questions and tests. The primary outcome is the proportion of spontaneous preterm deliveries before 34 weeks of gestation. A sample size of 254 pregnant women will be included at 29 participating hospitals in order to demonstrate noninferiority of placing a pessary versus vaginal progesterone. The first patient was randomized in August 2012, and recruitment of study subjects will continue until the end of December 2015.

**Discussion:**

This trial assesses the comparative efficacy and safety between two accepted treatments, cervical pessary versus vaginal progesterone, and it will provide evidence in order to establish clinical recommendations.

**Trial registration:**

EU Clinical Trials Register EudraCT2012-000241-13 (Date of registration: 16 January 2012); ClinicalTrials.gov Identifier NCT01643980 (Date of registration: 12 June 2012).

## Background

Preterm birth, defined as birth before 37 weeks of gestation, is the second most frequent direct cause of infant death in children younger than 5 years old [1–4]. Preterm birth is considered a major problem in modern Obstetrics, and it is the leading cause of perinatal morbidity and mortality in developed countries [5]. It is also associated with an important economic burden [6, 7]. Despite significant medical advances, the rate of prematurity has not declined over the past 40 years; rather, it has continued to rise. An increase in maternal age and underlying maternal health problems, such as diabetes and hypertensive disorders or iatrogenic factors like greater use of infertility treatments, which lead to increased rates of multiple pregnancies and changes in obstetric practices (such as more caesarean births before term) [8] have been identified as different reasons that explain this phenomenon. The prevalence of preterm births is about 12 to 13 % in the United States of America and 5 to 9 % in the European Union and other developed countries [5]. Although all deliveries before 37 weeks of gestation are considered preterm, the highest proportion of complications and neonatal death occur in those born at less than 34 weeks.

In order to reach an effective decrease of prematurity, two premises are necessary: to identify pregnant women who are at risk and to dispose of measures that serve to extend pregnancy, thus avoiding the prematurity. Some published papers describe sonographic measurement of the cervix at the 16th week as a method of screening to detect women at risk of spontaneous preterm delivery [3, 9–11]. In 1996 [1], Iams et al. demonstrated that the risk of preterm delivery is inversely proportional to the length of the cervix on transvaginal ultrasonography (US) between 24 and 28 weeks of gestation in a nonselected population in the United States of America.

After this publication [1], several studies have shown that the risk of preterm birth was inversely correlated to the length of the cervix as measured by transvaginal ultrasound [2, 3, 9, 12, 13], which has been confirmed in a recent meta-analysis [14].

Therefore, considering that the risk of prematurity is inversely proportional to cervical length, cervical measurement constitutes a method of screening for use in pregnant women who are asymptomatic before 24 weeks [15–17]. For decades, different types of therapeutic intervention have been explored in order to decrease preterm births, including primary prevention measures (all pregnant women), secondary prevention measures (only in women at risk) or tertiary prevention measures (initiated after the delivery process has started) [18]. A recent review concluded that there was insufficient evidence to provide sound recommendations for clinical practice in approximately half of the evaluated interventions [19]. Nevertheless, according to several trials and systematic reviews, two strategies, vaginal progesterone [20–28] and silicon cervical pessary [29–32], have been shown to be effective at decreasing the rate of spontaneous delivery before 34 weeks of gestation in at-risk women who have a short cervix.

Progesterone is a key hormone during gestation that has uterus-relaxing effects. Low levels of progesterone are associated with a high grade of cervix maturation and, consequently, a shorter cervical length and a higher risk of spontaneous delivery. The administration of progesterone supplements decreases preterm delivery in women with a short cervix [20–23] and in pregnant women with a history of preterm births [25, 26].

In March 2012, Romero et al. published a meta-analysis [27], which explored whether the use of vaginal progesterone in asymptomatic women whose ultrasound showed a short cervix (under 25 mm) in the second trimester reduced the risk of preterm birth and improved neonatal morbidity and mortality.

Five relevant clinical trials, which included a total of 775 women and 827 infants, were analyzed. The results showed that treatment with vaginal progesterone was associated with a significant reduction in the preterm birth rate before 33 weeks (12.4 % versus 22.0 %; relative risk (RR) 0.58; 95 % confidence interval (CI), 0.42 to 0.80), <35 weeks (RR, 0.69; 95 % CI, 0.55 to 0.88), and <28 weeks (RR, 0.50; 95 % CI, 0.30 to 0.81); respiratory distress syndrome (RR, 0.48; 95% CI, 0.30 to 0.76); composite neonatal morbidity and mortality (RR, 0.57; 95 % CI, 0.40 to 0.81); birth weight <1500 g (RR, 0.55; 95 % CI, 0.38 to 0.80); admission to neonatal intensive care unit (RR, 0.75; 95 % CI, 0.59 to 0.94); and requirement for mechanical ventilation (RR, 0.66; 95 % CI, 0.44 to 0.98). There were no significant differences in the rate of adverse maternal events or congenital anomalies between the vaginal progesterone and placebo groups. The authors concluded that the data provides sufficient evidence about the benefit of vaginal progesterone to prevent the preterm birth in women with a sonographic short cervix. They recommend measuring cervical length using transvaginal sonogram at 19 to 24 weeks of gestation.

Although cervical pessaries were introduced for management of cervical incompetence [33–35] at the end of the 1950s, a very limited number of papers regarding the use of pessaries in pregnant women have been found. In a case control study, Arabin et al. [29] observed that the prematurity rate significantly decreased in singleton and twin pregnancies in women with a short cervix in comparison with the controls when pessaries were used.

The first randomized study using a pessary (PECEP trial) was published in 2012 [30]. A total of 385 pregnant women with singleton pregnancies and a cervix length of ≤25 mm detected through vaginal ultrasonography at 18 to 22 weeks of gestation were randomized (1:1) to cervical pessary or expectant management. A significant reduction (76 %) in spontaneous deliveries before 34 weeks was found in the pessary group (6.3 % versus 26.8 %; odds ratio 0.18, 95 % CI 0.08 to 0.37; *P* <0.0001). In addition, a decrease in low-weight neonates (<2500 g) was detected (6.3 % versus 29.5 %; odds ratio 0.23, 95 % CI 0.12 to 0.43; *P* <0.0001). After the PECEP publication, it was suggested [31] that more studies are needed in different settings to confirm the results of this single trial.

Finally, regarding safety, it is worth highlighting that natural, micronized vaginal progesterone is a medicine that can be administered either orally or vaginally. There are no described adverse reactions in the product monograph when it is administered vaginally. Some women have reported a slight increase in vaginal discharge [36]. Cervical pessary can produce an increase in vaginal discharge, but without an increase in bacterial vaginosis or corioamnionitis in pregnant women. Although slight discomfort can sometimes occur during pessary placement, most patients note that the discomfort is acceptable [30].

Because of the published data, ultrasound measurement of the cervix is being progressively incorporated into clinical practice and either pessary or progesterone is increasingly being used in women with a short cervix. However, there is a “therapeutic hole” and neither of the two strategies is approved for this indication. In order to clear up any doubts about the potential benefits of both treatments and to establish clinical recommendations, comparative data are necessary. Alfirevic et al. [37] compared three different cohorts using cervical pessary, vaginal progesterone or cerclage for women with a singleton pregnancy and a high risk of preterm birth due to a prior spontaneous preterm birth before 34 weeks and a shortened cervical length as detected by transvaginal ultrasound. Their data suggests that the three treatments are a reasonable option in this population and they concluded that direct randomized comparisons of these strategies are needed.

The main objective of the PESAPRO trial is to compare the efficacy of two treatments, vaginal progesterone and cervical pessary, in terms of decreasing the rate of spontaneous preterm births before 34 weeks of gestation in women with a short cervix, which has been detected by transvaginal ultrasonography.

## Methods/Design

PESAPRO is a noncommercial, national, multicenter, randomized, open-label trial designed to compare the effect on premature birth prevention of two currently accepted strategies: administration of progesterone (vaginally) or the placement of vaginal pessaries in pregnant women with a short cervix (≤25 mm) as diagnosed by transvaginal ultrasonography (US) in the second trimester morphology ultrasound.

The inclusion of a third arm with placebo control was discussed in the original design because it would have been a valuable tool from a methodological point of view.- However, it was later discarded due to ethical and feasibility issues after taking into consideration the most recent publications.

### Participating centers

Thirty-one hospitals are currently participating in the PESAPRO trial. Fourteen center had initially been invited to participate, and, later, 17 additional hospitals were incorporated into the trial in a second phase.

All participating Obstetrics Units routinely perform transvaginal ultrasonography in the second term as a screening diagnosis method to detect women at risk of preterm birth (listed in Appendix 1).

### Study population and trial development

Pregnant women with a short cervix (≤25 mm) as identified by routine transvaginal ultrasonography at 19 to 22 weeks of gestation are eligible to enroll. Before the evaluation, the woman should have an empty bladder and be placed in the dorsal lithotomy position. The vaginal probe should be placed in the anterior fornix without pressure. Initial orientation is established by locating the sagittal view of the cervix. The length of the endocervical canal should be measured in a straight line from the internal to the external cervix. The cervix is dynamic; therefore, three measurements should be made over a 3-minute period, and the shortest measurement reported for clinical use [16, 38]. During this routine ultrasonography in the second term, singleton-pregnancy women with a short cervix (≤25 mm) are considered to participate in the PESAPRO trial. Table 1 shows the inclusion and exclusion criteria. A member of the research team informs the patient about the clinical trial during this (second trimester ultrasound) visit or at a different time, according to investigator criteria. Once informed consent has been obtained and baseline data has been collected (demographic, medical and obstetric history, vaginal and endocervix samples for culture), participants are individually randomized to vaginal progesterone or pessary. Study participants are evaluated every four weeks (±7 days) for a total of four visits; routine assessments (such as blood pressure, and weight), cervicometry and fetal ultrasonography are performed during each visit to assess adverse events and compliance with the study medication (in the progesterone group). Women are asked to return unused study medication from the previous 4 weeks and compliance is determined on the basis of the amount of the study drug that is unused. Study treatments continue until the third term (37 to 37 + 4 weeks), when the obstetrician removes the pessary, collects all the leftover medication, or until delivery, whichever occurs first.

**Table 1 Tab1:** Inclusion and exclusion criteria for PESAPRO

Inclusion criteria	Exclusion criteria
• Women older than 18 years old	• Major fetal and/ or uterine abnormalities
• Pregnant women with a short cervix (<25 mm) identified by the use of routine transvaginal ultrasonography at 19 to 22 weeks of gestation	• Placenta previa during current pregnancy
• Gestational age at randomization between 20 weeks + 1 and 23 weeks +6	• Vaginal bleeding or ruptured membranes in the moment of randomization
• Single pregnancy	• Cervical cerclage *in situ*
• Women sign informed consent according to the GCP and local legislation	• History of cone biopsy
	• History of three or more premature labor
	• Allergic to peanut
	• Contraindication for progesterone usage
	• Active treatment with progesterone at randomization
	• If in an investigator’s opinion, there are findings on physical examination, abnormalities in the results of clinical analyzes or other medical factors, social or psychosocial that could negatively influence
	• Women unable to give the informed consent

Any patients who develop preterm labor during the study are treated according to the standard practice of the participating institution. The study treatments continue during hospitalization until the moment at which delivery is unavoidable or until completion of gestation is indicated. One additional assessment (medical record review or phone call) is performed 4 to 6 weeks after delivery in order to collect full data. See Table 2 for the detailed schedule of enrollment and assessments.

**Table 2 Tab2:** Schedule of PESAPRO study’s visit

	Visit 1 (Routine control 2 term)^a^	Inform Visit	Visit 0 basal (20 weeks + 1 to 23 weeks + 6)	Visit 1 (V0 + 4 weeks)	Visit 2 (V1 + 4 weeks)	Visit 3 (V2 + 4 weeks)	Visit 4 (EOT) (37 weeks to 37 weeks + 4)	Post-delivery visit (4 to 6 weeks post-delivery)
Eligibility criteria		**√**	**√**					
Informed consent			**√**					
Randomization and start of treatment			**√**					
Blood pressure/ weight			**√**	**√**	**√**	**√**	**√**	
Vaginal culture			**√**					
Manual vaginal exam			**√**				**√**	
Cervicometry	**√**		**√**	**√**	**√**	**√**	**√**	
Follow-up Questionnaire				**√**	**√**	**√**	**√**	
Basic fetal US			**√**	**√**		**√**	**√**	
End of treatment (EOT)							**√**	
Review maternal medical history			**√**					**√**
Review neonate medical history								**√**

^a^This visit is a routine (“standard of care”) visit in the control of pregnancy. Patients with a short cervix are invited to an extra visit (for information) before being enrolled in the study

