### Study outcomes

The primary outcome measure is the proportion of spontaneous preterm birth before 34 weeks of gestation. The secondary outcomes are the following: proportion of spontaneous preterm birth before the 37th and 28th weeks, the rate of premature rupture of membranes before 34 weeks, the neonate’s weight at birth, the rate of fetal intrauterine mortality during the treatment period, the rate of neonatal morbidity and mortality, the need for hospitalization and tocolysis treatment, the rate of chorioamnionitis during the third term, symptomatic vaginal infections during the treatment period and the proportion of participants with adverse events.

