#### Coordination and conduct of the trial

The study is coordinated by the Obstetrics and Gynecology Unit and the Clinical Pharmacology Unit (Appendix 2). Three investigator meetings have been held in order to review the study protocol and data collection in the electronic case report form (eCRF). Additionally, after the necessary approvals were obtained, a meeting was held in each hospital before the start of patient recruitment procedures. All documents required for the study are available at each participating site. The eCRF is a secure, interactive, web-response system available at each study center, provided and managed by the Biostatistics and Data Management Core Facility of Institut d’investigacions Biomèdiques August Pi i Sunyer (IDIBAPS) - Hospital Clínic, Barcelona.

In each participating Obstetrics Unit, the physicians and research personnel (research nurse or assistant) are in charge of patient screening and inclusion, ensuring compliance with the study protocol and collecting the study data in the eCRFs. The trial is being monitored by an independent monitor. The monitor regularly reviews the eCRFs, ensuring compliance with the trial protocol, data completeness and data accuracy. All adverse events and serious adverse events are being recorded according to standard procedures.

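### The only neonatal data review falls 4 to 6 weeks after delivery, when infants born before 28 weeks may still be in hospital, so later morbidity and in-hospital deaths may be missed

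*Protocol article*

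**What the plan says.** All references are to the protocol article.

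- **Outcome.** *Study outcomes* lists "the rate of neonatal morbidity and mortality" among the secondary outcomes. It gives neither components nor a time limit.
- **Collection.** *Study population and trial development* states: "One additional assessment (medical record review or phone call) is performed 4 to 6 weeks after delivery in order to collect full data". In Table 2 of that section the row "Review neonate medical history" has one tick, in the post-delivery column. No column follows it.
- **Very early births are foreseen.** The secondary outcomes include the "proportion of spontaneous preterm birth before the 37th and 28th weeks". Table 1 sets "Gestational age at randomization between 20 weeks + 1 and 23 weeks +6", so delivery before 28 weeks can occur on study.
- **Where the risk lies.** The *Background* says that "the highest proportion of complications and neonatal death occur in those born at less than 34 weeks".
- **Other route for late events.** *Coordination and conduct of the trial* says: "All adverse events and serious adverse events are being recorded according to standard procedures". It gives no duration and does not mention newborns.

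**The concern.** The single review is tied to time since birth, not to discharge or to a postmenstrual age. For an infant born at term, 4 to 6 weeks is a reasonable point at which to close the newborn record. For an infant born before 28 weeks, the same interval ends well short of term, and the hospital stay may not be over. A review meant to gather complete data cannot be relied on to do so for these infants.

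The window also lets the length of observation vary by two weeks between infants. *Statistical analysis* assigns Fisher's exact test to the remaining categorical variables. That test compares simple proportions and makes no allowance for unequal or truncated observation.

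At stake is how completely one secondary outcome is ascertained, in the infants whom the article itself regards as at highest risk.

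**Working it through.** **Inputs.** Review at 4 to 6 weeks after delivery (*Study population and trial development*, Table 2). Births before 28 weeks as a listed outcome (*Study outcomes*). Sample size 254, or 127 per arm (*Statistical analysis*). The rate of birth before 28 weeks is not in the documents and is assumed to be 1 to 5 %.

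**Step 1: the plan's own figure.** The sample size is used here only as a multiplier, but it reproduces. With planning rates of 12.4 % and 6 %, a margin of 4 %, one-sided alpha of 2.5 % and power of 80 %:

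n per arm = (1.96 + 0.84)² × (0.124 × 0.876 + 0.06 × 0.94) / (0.04 + 0.124 − 0.06)², which rounds up to 120.

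Allowing for 5 % drop-out: 120 / 0.95 = 126.3, so 127 per arm and 254 in total, as stated.

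**Step 2: maturity at the review.** Postmenstrual age at review = gestational age at birth + 4 to 6 weeks.

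| Born at | At 4 weeks | At 6 weeks |
|---|---|---|
| 24+0 | 28+0 | 30+0 |
| 27+6 | 31+6 | 33+6 |
| 30+6 | 34+6 | 36+6 |

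Every infant born before 28+0 is therefore below 34+0 at last data collection. Any infant born before 31+0 is still below 37+0 even at the 6-week limit (31+0 + 6 weeks = 37+0).

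**Step 3: what the window does cover.** 4 weeks × 7 = 28 days and 6 weeks × 7 = 42 days. A review at the earliest limit already spans 28 days, so deaths within 28 days can be recorded for every infant. Deaths between day 28 and day 42 are caught or not according to when the review happens. Deaths after the review are outside the schedule.

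**Step 4: how many infants.** 254 × 1 % = 2.5 and 254 × 5 % = 12.7, so about 3 to 13 infants over both arms. The upper end is generous. The planning rates imply 127 × 6 % = 7.6 and 127 × 12.4 % = 15.7 births before 34 weeks, 23.4 in all, and 12.7 / 23.4 = 54 % of them would have to fall before 28 weeks. Only infants alive and still in hospital at the review can have later in-hospital events, so the number with an incomplete record is lower again.

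**Step 5: length of the gap.** For a birth at 24+0, 40 weeks' postmenstrual age is reached 40 − 30 = 10 to 40 − 28 = 12 weeks after the review.

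**The case against.** The strongest reply is that the outcome is called neonatal. If that means the first 28 days (an assumption, since the article gives no definition), a review at 28 to 42 days closes at or after the end of that period for every infant, whatever the gestation at birth. On this view, asking for data to discharge replaces one endpoint with another. This stands for mortality within 28 days. It does not settle morbidity: the article sets no time limit, names no components, and describes the contact as the one that completes the data.

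A second reply is that the full protocol or case report form may define the components and follow infants still in hospital. It may. But the article does more than stay silent. It fixes one review at one time, and that timing is the point at issue.

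A reader might infer more than the documents support:

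- *That late events are scored as absent.* No section says how an infant still in hospital at the review is coded, or that the record is then closed. The article shows no planned route for later events; it does not state that they are excluded.
- *That every very preterm infant has an incomplete record.* Infants who died, went home or had their complications diagnosed before the review have those events on record.
- *That the arms are made to look more alike.* The window is the same in both arms. Equal under-detection shrinks an absolute difference but need not change a risk ratio. Unequal loss requires an imbalance in very early births, and that would show in the separate outcome of birth before 28 weeks.
- *That the trial's main conclusion depends on this.* The main objective, the primary outcome and the sample size all rest on birth before 34 weeks.

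**Conclusion.** The point holds as a minor one. A single review 4 to 6 weeks after delivery reaches infants born at 24+0 to 27+6 at 28+0 to 33+6 weeks' postmenstrual age. Morbidity diagnosed later, and in-hospital death after the review, may be missed.

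This rests on two assumptions: that some of these infants are still in hospital at the review (the documents give no length of stay), and that the undefined morbidity outcome includes conditions that can be diagnosed after it. The count of about 3 to 13 infants rests on an assumed rate and is best read as an upper range. This is a cheap improvement to the ascertainment of a secondary outcome, not an error that threatens the trial.

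**What to change.** For any infant still in hospital at the 4-to-6-week review, repeat the record review at discharge or at 40 weeks' postmenstrual age, whichever comes first. Report morbidity and in-hospital mortality to that end point, alongside mortality at a fixed 28 days, and state these time limits in the outcome definition. The fixed 28-day figure also removes the effect of the two-week spread in review dates on mortality.

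The cost is a second chart review for a few infants and an added date in the case report form. The data lock could move by up to about 3 months for the last very preterm births (the 10 to 12 weeks of Step 5). In practice the delay may be shorter: a woman at the same gestation on the same date who delivers at 37+0 is herself reviewed at 41+0 to 43+0, after the 40-week point. Sample size, primary analysis and treatment are unchanged.
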